#### Primary outcome

*Restrictions for social and work-related participation* will be captured with the IMET [42]. This validated questionnaire determines the impairment of persons with a chronic disease by the International Classification of Functioning, Disability and Health (ICF). The IMET imposes restrictions on participation in nine relevant dimensions in everyday life. The appraisal for each dimension is based on a scale from 0 to 10, and it is possible to analyse single items as well as the cumulative score. High scores implicate highly restricted participation. The IMET is a validated questionnaire for chronically ill patients [43, 44].

*Breast cancer-specific quality of life* will be measured with the EORTC-QLQ-BR23 [45]. The Quality of Life Questionnaire BR23 is an additional module from EORTC-QLQ-C30 that was developed for use in patients with breast cancer in different disease stages and with different types of therapy. The items include side effects from the systematic forms of therapy, such as arm symptoms, breast symptoms, body image, and sexual functions, and single items, such as sexuality, loss of hair, and future perspectives. All of these subscales can be ranked between 0 and 100 points. A higher score induces a better function and a higher quality of life. In the system subscales, a higher score signifies a higher level of symptoms and problems [45]. The QLQ-BR23 is a validated, reliable questionnaire used in numerous studies.

*Return to work* will be captured in a retrospective way with two single items. The rehabilitants are asked whether they returned to work after rehabilitation, and if so, how much time (in months) passed between rehab and return to work.

#### Secondary outcomes

After medical rehabilitation, a great number of patients return to work without major problems [46, 47]. To include the work-related effects from this study, further work-related outcomes will be considered.

*Work ability* will be measured with the Work Ability Score (WAS) of the Work Ability Index (WAI). This single item consists of work ability on a scale from 0 to 10, and a higher score indicates higher work ability. The WAS has been applied in numerous studies and has acceptable reliability and validity [48].

*Occupational stress* will be measured with the German version of SIBAR II and IV, and the overall burden and differentiated single burdens will be addressed [49].

The SPE scale in the German language considers the *subjective prognosis of gainful employment*. Three items estimate the occupational risk of the patients. Adding the single items to form a total score, the patients can be subdivided into two risk groups. This scale has been validated in a large sample and is also reliable. Thus, the items have a good ability to obtain the subjective prognosis of gainful employment [50, 51].

*Occupational changes* will be measured with single items, including job-preserving interventions and types of job loss [52].

Cancer-related *fatigue* will be measured by the EORTC-FA12, a questionnaire validated in a large international, multicentre study [53]. With the aid of twelve four-staged items (“not at all” to “very”), physical, emotional, and cognitive fatigue impairments are investigated. During a German study validating the questionnaire with breast cancer patients [54], a high consistency of the overall scale was observed; the subscale also shows good to high internal consistency.

*Depressive state* will be measured by the CES-D (Center for Epidemiological Studies Depression Scale, German version). The scale consists of 20 four-level scaled items regarding the presence and frequency of depressive symptoms. The evaluation is made according to a total score that can reach a maximum of 60 points. The higher the value is, the higher the expression of depressive symptoms. The CES-D is a reliable and valid questionnaire [55].

The *performance* in various areas of life will be assessed by three scales from 0 to 10 for the areas job, everyday life, and leisure. A high score implies high performance. The three single items are approved as a valid procedure for the determination of performance restrictions [52, 56].

The extent of *physical activity* will be assessed in connection with the questionnaire of the Federal Health Survey by Menski, 1998 [57]. In addition, the use of health promotion services will be measured by a questionnaire from the Quality Community for Medical Rehabilitation [52, 56].

The moderating variable is comorbidity [58], as well as risk factors and sociodemographic variables [59]. Table 1 shows the set of the core instruments to be used in the study.

**Table 1 Tab1:** Core set of instruments used in the quantitative part of the study

Dimensions	Instruments	t_0_	t_1_	t_2_
Primary Outcome				
Restriction of Participation	IMET [42]	●		●
Disease-specific Quality of Life	EORTC-QLQ-C30 [60]	●	●	●
	EORTC-QLQ-BR23 [45]			
Return to Work	Single Items			●
Secondary Outcomes				
Ability to Work	Work Ability Score, WAS [61]	●		●
Occupational Stress	SIBAR, II and IV [49]	●		●
Subjective Prognosis of Employment	SPE-Scale [62]	●		●
Occupational Changes	Single Items from QGmR [52]			●
Fatigue	EORTC-FA 12 [54]	●	●	●
Depressive State	CES-D [55]	●	●	●
Performance in Various Areas of Life	QGmR [52]	●		●
Physical Activity	Federal Health Survey [57]	●		●
Use of Health Promotion Services	QGmR [52]	●	●	●
Moderating Variables				
Comorbidity	Single Items [58]	●		●
Living Habits	Single Items	●	●	●
Sociodemographic Data	Single Items [59]	●		●

t_0_ = baseline/right before rehabilitation; t_1_ = 3-week follow-up/right after rehabilitation; t_2_ = 12 months after t_1_

Outcomes that cannot change during rehabilitation will be measured in the beginning and regard only catamnesis. These include outcomes regarding everyday life and the domestic environment of the patients (social participation, efficiency and physical activity in daily life) or insignificantly changed outcomes, such as medically determined comorbidities.

### B: qualitative measures

#### Interviews and focus groups with patients, aftercare agents and physicians

Six rehabilitants will be interviewed by telephone at 3, 6 and 9 months post-rehab. From their personal point of view, they should assess the aftercare strategy, the use of ReNaApp, and the current status of the aftercare programme. At the time of catamnesis and written surveys, the interviewees will be asked about the utility of the app and their acceptance of and satisfaction with the use of ReNaApp. In addition, the patients will express their wishes and record them for further development or optimization of the mobile application and aftercare strategy. The interviewees will differ in age and education to assemble a heterogeneous group as much as possible [63].

At the end of recruitment, several focus groups will be carried out with the aftercare agents and involved physicians of the five clinics. These focus groups will discuss the feasibility and practicability in clinical practice, the optimization possibilities, and the level of patient support provided by the ReNaApp.

All interviews and focus groups follow a guideline. The guidelines and the results of the qualitative assessment will be presented and discussed within the project team and in the interdisciplinary expert forum “Arbeitsgruppe qualitativer Methoden” (AQUAM; Working group on qualitative methods). The interviews will take approximately 30 min, while the focus groups will be longer. With the approval of every participant, the interviews and focus groups will be recorded and transcribed word by word. The subsequent evaluation will be performed according to the qualitative content analysis.

### C: formative evaluation of the mobile application

Generating a high usability is the main focus during the development of ReNaApp. More than 10 patient representatives (breast cancer patients) will receive the developed prototypes of ReNaApp and execute exemplary tasks, i.e., documenting physical activity in the diary.

The interactions with the system (prototype) have to be evaluated by objective data (processing time and accuracy, human mistakes), subjective information about satisfaction and acceptance (e.g., QUIS [64], UTAUT [65]) and mental demand (NASA-TLX [66]). Furthermore, problems due to the interaction with the system need to be discussed. Positive evaluated aspects of the design will be integrated into the development of the overall system.

### D: health economic evaluation

The aim of the health economic evaluation of ReNaApp is to determine the cost-effectiveness of the motion-based aftercare programme for women with breast cancer using an app (intervention group: IG) against the cost-effectiveness of a standardized rehabilitation measure with standard aftercare (control group: CG). Quantitative methods will be used to identify which intervention is more beneficial from an economic perspective. In addition, qualitative methods will be used to gain insights about factors that may enable or hinder aftercare implementation in rehabilitation clinics.

The standardized implementation of health economic studies requires the consideration of various conceptual and methodological aspects.

#### Data basis

The basis of this analysis comprises data of the primary and secondary outcomes of the rehabilitation surveys at t0 and t2, supplemented by questions regarding service consumption and other benefit parameters. Standardized patient questionnaires will be used for assessment, as well as the costs of intervention implementation in the facilities by means of structured interviews with rehabilitation facilities’ staff.

#### Types of health economic analyses

Proof of the advantage of the new intervention (rehabilitation model “Neues Credo” plus rehabilitation aftercare app) over the standard intervention in use (standard rehabilitation plus standard aftercare) will be provided by cost-effectiveness analyses, in which the effect parameters will be included in natural units (e.g., return to work) and via standardized and weighted uniform utility values (e.g., quality of life) [67–69]. Pre-post changes will be compared for the IG and the CG. The differences are called incremental costs, i.e., incremental effects. The result is shown as the ratio of incremental costs and the respective incremental benefit parameter [67]. An unfavourable effectiveness ratio can be caused by both low clinical effectiveness and high costs. A clinically less effective measure can also have superior cost-effectiveness if it offers high savings potential compared to the alternative procedure.

In addition, so-called cost-utility analyses will be carried out based on quality adjusted life years (QALYs). Here, the intervention-induced change in health status will be evaluated with health-related quality of life (QoL) measures, e.g., QALYs. QALYs are interpreted as an index for lifetime gain and QoL - a QALY represents 1 year of life in optimal health [70]. The incremental costs per QALY allow comparison with other breast cancer treatment interventions (EORTC-QLQ-C30 and -BR23) and with other indications (SF12) [67, 71, 72].

#### Perspectives of the study

The selection of relevant cost components is derived from the study hypothesis and the respective study perspective. For all studies, it is recommended that the analysis be carried out from a societal perspective to present the relevant benefits and resource consumption at a macroeconomic level. Additionally, the results that are relevant for the cost bearers (here: pension insurance institutions) should be added to describe possible divergences between the societal and cost bearers’ perspectives. The perspective of the patients is taken to identify possible influencing factors regarding consumption behaviour. Depending on the perspective, different exclusions are made for the cost and benefit parameters [67].

#### Cost parameters of the study

In health economic evaluations, a distinction is made between direct and indirect costs. By definition, direct medical and non-medical costs include the consumption of resources by health care sectors and patients or their social environment that are directly attributable to the disease or impairment and valued in monetary units.

For the ReNaApp study, the expected cost savings for both study groups from reduced service use in the 12 months after rehabilitation compared to the 12 months before rehabilitation (= net costs) will be determined. The difference between CG net costs and net costs, including the additional costs from the use of the new aftercare app (IG), will yield incremental costs.

All patients will document volume data of the utilization of services in the questionnaires.

Due to the lack of market prices, the evaluation of this database will be mainly based on prices administered by the state or agreed upon by association [67–70, 73]. The recommendations for determining valuation rates in health economic evaluation [74] will be considered as much as possible and supplemented by currently published billing approaches, e.g., [75–77].

To fully determine the costs from a societal perspective, co-payments, deductibles or other forms of co-payment to be made by patients, as well as costs incurred outside the social insurance system, (e.g., in the form of patients’ own contributions for non-reimbursable health care services and support services provided by the social environment), will also be included.

Indirect costs reflect the loss of value added due to the illness, valued in monetary units. From a pension insurance perspective, expenditure on rehabilitation and aftercare represents investments in maintaining earning capacity. To this extent, benefits for temporary and permanent reduction in earning capacity should be highlighted here. Costs arising from periods of incapacity to work on the part of the health insurance funds (sick pay) and employers (continued wage payments) and income losses from reduced working hours without financial compensation by the social insurance funds, e.g., reduced earning capacity pensions for female patients, are further cost items to be included. From a societal perspective, lost social security contributions also need consideration. In addition to these work- and employment-related productivity losses, ReNaApp accounts for reductions in performance in private life (e.g., housework, leisure time, voluntary work) to complete the patient perspective.

Two valuation approaches - the human capital approach (HCA) and the friction cost approach (FCA) - are available for determining the costs associated with the performance and productivity reductions. Both reflect the societal perspective, but they account for productivity losses differently. The controversial discussion about the two methodological approaches has not been resolved, so the recommendation to apply both approaches and examine the different outcome effects in sensitivity analyses is followed [67, 68]. Both approaches tend to neglect non-work activities (household, child-rearing, voluntary work, leisure time, etc.). Since it is to be expected that a significant proportion of the ReNaApp target population is already of pensionable age, the limited recording of indirect costs for the periods up to retirement can constitute discrimination. In this respect, a sensitivity analysis is additionally carried out based on the average remaining life expectancy [78].

For the assessment of the loss of value added due to sickness-related absence from work, the average gross annual income from dependent employment for the total working population [74] is applied to obtain results independent of indications.

#### Investment costs

Regarding the inclusion of intervention costs in health economic evaluation, different positions are held in the literature (see [67]). For the ReNaApp study, therefore, intervention costs are not included in the cost-effectiveness analysis or in the cost-utility analysis. They are used exclusively to determine a possible break-even point for the minimum number of patients necessary to cover the costs of the developmental intervention.

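### The health economic evaluation counts the costs of using the app in incremental costs, yet as worded excludes intervention costs from both economic analyses; the scope of the exclusion must be stated

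*Protocol article*

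**What the plan says.** All of the text is in the protocol article, component D (health economic evaluation).

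- **Cost parameters of the study.** Net costs are formed in each group from the change in service use between the 12 months before and the 12 months after rehabilitation. The difference between control group (CG) net costs and IG net costs, "including the additional costs from the use of the new aftercare app (IG), will yield incremental costs".
- **Types of health economic analyses.** Incremental cost is the numerator of the result: "The result is shown as the ratio of incremental costs and the respective incremental benefit parameter". The cost-utility analysis uses the same numerator, and its result is meant to travel beyond the trial: "The incremental costs per QALY allow comparison with other breast cancer treatment interventions".
- **Perspectives of the study.** For all studies "it is recommended that the analysis be carried out from a societal perspective", with the cost bearers' view added.
- **Data basis.** The data include questionnaires, "as well as the costs of intervention implementation in the facilities by means of structured interviews" with clinic staff.
- **Investment costs.** After noting that positions in the literature differ, the section concludes that "intervention costs are not included in the cost-effectiveness analysis or in the cost-utility analysis". It continues: "They are used exclusively to determine a possible break-even point for the minimum number of patients" that is "necessary to cover the costs of the developmental intervention".

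**The concern.** The cost of using the app is a cost of the intervention. It cannot be in the numerator of the cost-effectiveness ratio and, at the same time, belong to a class of cost kept out of that analysis. An analyst following the section on cost parameters and one following the section on investment costs would produce different ratios from the same data, and the choice could be made after the results are known.

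Incremental cost enters every ratio in component D, so the question reaches all of them. If the exclusion is applied as worded, the IG is credited with any savings while being charged nothing for the programme that is supposed to produce them. That also sits badly with the recommended societal perspective.

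The only reason given for the exclusion is that the literature is divided. In the section on cost parameters, the plan meets another unresolved dispute, human capital versus friction cost, and there applies both approaches in sensitivity analyses.

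**Working it through.** The protocol states no intervention cost, ICER or break-even figure, so there is no figure to reproduce. The check is a comparison of the sections, followed by algebra.

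**Step 1: where each cost goes.** The broad reading takes the Investment costs section as worded. The narrow reading limits it to one-off development cost.

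| Cost of the IG programme | Cost parameters section | Investment costs, broad reading | Investment costs, narrow reading |
|---|---|---|---|
| Use of the app | counted | excluded: conflict | not excluded: consistent |
| Delivery in the clinics (agent and therapist time, group hour, observation book, letters; see Intervention section) | not named | excluded | assigned to no analysis |
| One-off app development | not named | break-even only | break-even only |

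The conflict exists on the broad reading. On the narrow reading it disappears, but the clinic delivery costs still have no stated place in the numerator. The Data basis section does not settle this: collecting implementation costs is compatible with using them for break-even, for incremental cost, or for both.

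**Step 2: effect of leaving a cost out.** Per patient, let

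- dS = IG minus CG difference in net costs, before any intervention cost;
- c = recurrent delivery cost of the IG programme, with c > 0;
- dE = incremental effect;
- λ = value placed on one unit of effect.

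With c excluded, ICER = dS/dE. With c included, ICER = (dS + c)/dE. For dE > 0 the exclusion understates the ICER by c/dE.

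Net monetary benefit is λ·dE − dS with c excluded and λ·dE − (dS + c) with c included. The exclusion overstates it by c, whatever the sign of dE and whatever λ.

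If −c < dS < 0, the programme appears cost-saving when c is excluded and is not cost-saving when c is included.

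Write c = a + b, with a for app use and b for clinic delivery. The broad reading omits a + b. The narrow reading omits b, if b is in fact left out.

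**Step 3: illustration with assumed values only.** Neither c nor dE is in the protocol. Assume c between EUR 50 and EUR 300 and dE between 0.01 and 0.05 QALY.

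- Smallest shift: 50/0.05 = EUR 1,000 per QALY.
- Largest shift: 300/0.01 = EUR 30,000 per QALY.
- One change of sign: with dS = −200, c = 300 and dE = 0.02, the ICER is −200/0.02 = −10,000 with c excluded and (−200 + 300)/0.02 = +5,000 with c included.

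The width of this range shows that the size cannot be inferred from the protocol. The direction does not depend on the assumed values.

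**The case against.** The best defence is that the Investment costs section concerns one-off outlay. Its heading says so. A break-even point expressed as a minimum number of patients makes sense mainly for a fixed sum, and the sum to be recovered is described as "necessary to cover the costs of the developmental intervention". Read that way, the section fits the one on cost parameters and the term used is merely loose. Whether development cost belongs in an ICER is also a matter on which methodologists differ, and the plan discloses its choice.

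Much of this stands. A reader might infer that the plan deliberately excludes every intervention cost and that its ICER is therefore biased. The document does not support that. It does not say that all such costs are excluded, and another section expressly counts the costs of app use.

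What does not stand is that the narrow reading settles the matter. No section draws the line between development and delivery. The section on types of analysis describes the new intervention as the whole package, the rehabilitation model plus the app, so intervention costs in the document's own terms are not confined to development. The narrow reading also leaves clinic delivery costs unassigned. The section on transferability does say that the clinics' only time burden is sending letters and answering questions where needed. This suggests a small cost after discharge, but it does not cover the group hour during rehabilitation or app operation.

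**Conclusion.** The point holds as a conflict of wording with a conditional bias. As written, the sections on cost parameters and on investment costs give different numerators, and the text does not state the narrower meaning that would reconcile them.

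If the exclusion is applied as worded, net monetary benefit is overstated by c and, given a positive incremental effect, the ICER is understated by c/dE. Both errors favour ReNaApp. With a zero or negative effect, the bias should be stated on net monetary benefit only. The size is unknown. If only development cost was meant and delivery costs are counted, the understatement set out here does not arise, and what remains is the disclosed choice to leave development cost out.

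The matter is confined to component D. The clinical comparisons of the three primary outcomes and the sample size are untouched.

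**What to change.** Reword the Investment costs section so that the exclusion covers only the one-off cost of developing the app, which is kept for the break-even calculation. State in the section on cost parameters that the recurrent delivery costs of the IG programme enter the IG costs of both the cost-effectiveness and the cost-utility analysis. These are agent and therapist time, the group hour, materials, letters and app operation. Optionally, add a sensitivity analysis that spreads development cost per patient.

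The clinic items can come from the facility interviews already planned under Data basis. App operating cost is not something those interviews are said to cover, so it has to be taken from project records. The cost of the change is a reworded paragraph, one extra cost item to obtain and a slightly less favourable ICER. It should be settled before the economic data are analysed.
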